## Confidentiality

The anonymized data will be collected in the standard data collection form. The confidentiality of the data will be maintained during, after the study and during publication of the results.

## Regulatory and Ethical Considerations

The study will follow all the principles laid down by Declaration of Helsinki.

The study will commence after approval from the Institutional Ethics Committee from the Central coordinating site (AIIMS Bathinda) and each participating site.

## Recruitment Strategy

The patient planned for elective surgery will be screened as per inclusion-exclusion criteria a day prior to the surgery. For emergency surgeries, the screening will be done as earliest possible before planned emergency surgery (general surgery or neurosurgery).

## Informed Consent/Assent

Since, the multimodal interventions are based on already existing guidelines by WHO and IDSA, there is no involvement of any new intervention/drug, the study is low-minimal risk. Thus, we will request the Ethics Committee (EC) for waiver of the informed consent for this study.

# PUBLICATION Plans

We plan to publish the protocol and the manuscript in the PubMed indexed journal preferably “Journal of Antimicrobial Chemotherapy” or “International Journal of Antimicrobial Agents”.

# TOTAL BUDGET (TOTAL for all 7 centers)

| **S.NO** | **Particulars cumulative of all 7 centers** | **Year 1** | **Year 2** | **Year 3** | | **Total 3 years** |
| --- | --- | --- | --- | --- | --- | --- |
|  | **Staff/ Manpower** for the duration of | 10 months | 12 months | 10 months | | 32 months |
|  | 1. Project Technical Support-III (**5% increment in 3^rd^ year**)   @ 28,000 + 9% HRA = ~30,520 INR per month per centre (*4 centres)  @ 28,000 + 18% HRA = ~33,040 INR per month per centre (*3 centres) | 3,05,200 * 4 = 12,20,800 INR  3,30,400*3= 9,91,200 | 3,66,240*4= 14,64,960 INR  3,96,480*3= 11,89,440 | 3,20,460* 4 = 12,81,840 INR  3,46,920*3= 10,40,760 | | 71,89,000 INR |
|  | 1. Project staff Nurse (Project Nurse-II) (**5% increment in 3^rd^ year**)   @ 20,000 + 9% HRA = ~21,800 INR per month per centre (*4 centres)  @ 20,000 + 18% HRA = ~23,600 INR per month per centre (*3 centres) | 2,18,000 * 4 = 8,72,000 INR  2,36,000*3= 7,08,000 INR | 2,61,600*4 = 10,46,400 INR  2,83,200* 3= 8,49,600 INR | 2,28,900 * 4 = 9,15,600 INR  2,47,800*3= 7,43,400 INR | | 51,35,000 INR |
|  | Subtotal | 37,92,000 | 45,50,400 | 39,81,600 | | 1,23,24,000 INR |
|  | **Justification of Staff/Manpower:** Although each department has nursing staff, but the dedicated nurse is not provided by institute for antimicrobial stewardship work or project purpose. The project will need a dedicated nurse for the project to spare visit to the OT area posted and follow up of patients as the follow up is 30-days post-surgery (or 90-days if implant in situ) | | | | | |
|  | **Equipment Name** |  |  |  |  | |
|  | Desktop with Multifunctional Printer | 70,000 + 40,000 per Centre (*7) |  |  | 7,70,000 INR | |
|  | **Consumables (Recurring)** |  |  |  |  | |
|  | Printing and stationary | 50,000 per Centre (*7) |  |  | 3,50,000 INR | |
|  | **Contingency** |  |  |  |  | |
|  | Article Publication Charges (APC) for 2-3 manuscripts expected | 2,50,000 |  | 2,50,000 | 5,00,000 INR | |
|  | Miscellaneous | 2,00,000 |  |  | 2,00,000 INR | |
|  | **Travel and Meetings** |  |  |  |  | |
|  | Physical meeting of all PIs/Co-PIs: 5 (one before starting the study, three during study and one after study completion) visit to centre for training/data compilation and TA/DA to all collaborators | 1,00,000 | 3,00,000 | 1,00,000 | 5,00,000 INR | |
|  | Prescription research and prescriber skill course (including training of the JRF and ICN for data collection) at the central coordinating site | 1,00,000 | 1,00,000 | 1,00,000 | 3,00,000 INR | |
|  | Re-training sessions |  | 1,00,000 | 1,00,000 | 2,00,000 INR | |
| 6. | **Overhead charges** (3% excluding travel and meetings, equipment, consumables) | 1,27,260 | 1,36,512 | 1,26,948 | 3,90,720 INR | |
|  | **Subtotal year wise** | 56,89,260 INR | 51,86,912 INR | 46,58,548 INR |  | |
|  | **Total budget of all seven centers for 3 years** | | | | **1,55,34,720 INR** | |

# Appendix-I: Template example of the components of Multipronged interventions and CheckLIST to be checked for each patient

The intervention components can be chosen based on observed practices in the clinical setting, gap analysis, the global guidelines for prevention of surgical site infections by WHO^2^, second edition 2018 and Clinical practice guidelines for antimicrobial prophylaxis in surgery which were recommended with “Strong” recommendations and “Moderate to Good” quality of evidence and easy to implement in the setting.

**Table-2:** Template intervention package (not necessarily the same interventions mentioned below)

| **Components of multipronged Intervention** | **Steps of the Intervention** | **Type of standardization** | **Limits of standardization** |
| --- | --- | --- | --- |
| Interventions for surgical infection prevention: four system interventions | Delivery of intravenous antimicrobial prophylaxis within 1 hour before incision (2 hour for vancomycin and fluoroquinolones) | Mandatory | Boundaries (Flexibility in choosing antimicrobial by the surgeon based on the type of surgery, patient factors, clinical practice and guidance documents) |
|  | Redosing of antimicrobial if interval >2 half-lives or if blood loss >1500 ml | Optional | Boundaries (Flexibility based on the duration of the surgery and type of the antimicrobial agent chosen for surgical prophylaxis) |
|  | Use of antimicrobial prophylactic agent consistent with published guidelines (Global guidelines for prevention of surgical site infections by WHO^2^, second edition 2018 and Clinical practice guidelines for antimicrobial prophylaxis in surgery^10^) | Mandatory | Boundaries (Flexibility in choosing antimicrobial by the surgeon based on the type of surgery, patient factors, clinical practice and guidance documents) |
|  | Discontinuation of prophylactic antimicrobial agent within 24 hours of surgery (within 48 hours for cardiothoracic procedures in adult patients): Post operative day- 1(POD-1) review | Mandatory | Flexibility allowed till 24 hours postoperative |
| Interventions for surgical care improvement: five behavioral interventions | Proper hair removal: No removal (if not hampering surgery) or use of clippers/depilator method. | Optional | Boundaries (Flexibility in choosing no removal or clippers or depilators) |
|  | Use of razors for hair removal | Prohibited (Considered inappropriate if razors used for hair removal) | Exactly (Not flexible) |
|  | Use of alcohol chlorhexidine based pre-operative skin preparation if no contra-indication exists and aseptic precautions including hand hygiene. | Optional (Based on availability and patient factors, alcohol chlorhexidine based or Povidone iodine-based solution can be used for skin preparation with proper drying) | Flexible based on availability and surgeon choice |
|  | Controlled blood glucose during immediate post-operative period. | Optional | Boundaries (levels blood sugar to be mentioned as controlled varies as per patient characteristics) |
|  | Maintenance of perioperative normothermia (≥35.5°C) in surgical patients | Optional (maintained if duration of anesthesia >60 minutes) | Exactly (Patients where therapeutic hypothermia needed will be excluded from the study) |
|  | Minimizing the door opening of the operating room | Optional | Flexible |

**Table-3: Template Checklist to be checked for each patient based on the components of the multipronged interventions co-developed by the stakeholders.**

| S.NO | Interventions |  | Intervention followed or not (Yes or No) |
| --- | --- | --- | --- |
| 1 | Delivery of intravenous antimicrobial prophylaxis within 1 hour before incision (2 hr for vancomycin and fluoroquinolones) | Time of antimicrobial prophylaxis administration…………..  Time of start of surgery…………………. |  |
| 2 | Redosing of antimicrobial if interval >2 half-lives or if blood loss >1500 ml | Redosing required or not …….  Duration of surgery ………… |  |
| 3 | Use of antimicrobial prophylactic agent consistent with published guidelines | Name of antimicrobial given as surgical prophylaxis …………………………. |  |
| 4 | Discontinuation of prophylactic antimicrobial agent within 24 hours of surgery (within 48 hours for cardiothoracic procedures in adult patients) | Time of stoppage of surgery……………  Time and date of last dose of antimicrobial prophylaxis …………………………….. |  |
| 5 | Proper hair removal: No removal (if not hampering surgery) or use of clippers/depilator method. Use of razors to be considered inappropriate | Hair removed or not ………  If yes, method of hair removal …………………………… |  |
| 6 | Use of alcohol chlorhexidine based pre-operative skin preparation if no contra-indication exists and aseptic precautions including hand hygiene. | Agent used for skin preparation……………….. |  |
| 7 | Controlled blood glucose during immediate post-operative period. | Blood sugar levels 6 hourly in postoperative period …………  …………………………… |  |
| 8 | Maintenance of perioperative normothermia (≥35.5°C) in surgical patients who have anesthesia >60 minutes | Temperature in intra-operative period ………….. |  |
| 9 | POD-1 review of antimicrobials. | Any advice given: ……………………………….  Advice followed or not? …………………………….. |  |
| 10 | SSI surveillance as per CDC/NHSN definition of SSI. | SSI surveillance done as per definition mentioned in Appendix-II …………….. |  |

# Appendix-II: who SURGICAL SITE INFECTION SURVEILLANCE POST-OPERATIVE DATA COLLECTION FORM

# Appendix-IiI: DIAGNOSIS OF SURGICAL SITE INFECTION AS PER CDC

| **Superficial incisional SSI :** Must meet the following criteria:  Date of event occurs within 30 days following the operative procedure (where day 1 = the procedure date) **AND** involves only skin and subcutaneous tissue of the incision  **AND**  patient has at least ***one*** of the following:   1. purulent drainage from the superficial incision. 2. organism(s) identified from an aseptically-obtained specimen from the superficial incision or subcutaneous tissue by a culture or non- culture based microbiologic testing method which is performed for purposes of clinical diagnosis or treatment (for example, not Active Surveillance Culture/Testing [ASC/AST]). 3. a superficial incision that is deliberately opened by a surgeon, physician* or physician designee and culture or non-culture based testing of the superficial incision or subcutaneous tissue is not performed **AND** patient has at least one of the following signs or symptoms: localized pain or tenderness; localized swelling; erythema; or heat. 4. diagnosis of a superficial incisional SSI by a physician. |
| --- |
| **Deep incisional SSI**  Must meet the following criteria:  Date of event occurs within 30 or 90 days following the operative procedure (where day 1 = the procedure date) **AND** involves deep soft tissues of the incision (for example, fascial and muscle layers) **AND** patient has at least ***one*** of the following:   1. purulent drainage from the deep incision. 2. a deep incision that is deliberately opened or aspirated by a surgeon, physician or spontaneously dehisces   **AND**  organism(s) identified from the deep soft tissues of the incision by a culture or non-culture based microbiologic testing method which is performed for purposes of clinical diagnosis or treatment (for example, not Active Surveillance Culture/Testing [ASC/AST]) or culture or non- culture based microbiologic testing method is not performed. A culture or non-culture based test from the deep soft tissues of the incision that has a negative finding does not meet this criterion.  **AND**  patient has at least ***one*** of the following signs or symptoms: fever (>38°C); localized pain or tenderness.   1. an abscess or other evidence of infection involving the deep incision detected on gross anatomical exam, histopathologic exam, or imaging test. |

# Appendix-IV: SURGICAL WOUND CLASSIFICATION AS PER CDC

| Surgical wound classification as per CDC definition^2,19^ | |
| --- | --- |
| Class I/ Clean | An uninfected operative wound in which no inflammation is encountered and the respiratory, alimentary, genital, or uninfected urinary tract is not entered.  In addition, clean wounds are primarily closed and, if necessary, drained with closed drainage.  Operative incisional wounds that follow nonpenetrating (blunt) trauma should be included in this category if they meet the criteria. |
| Class II/ Clean-Contaminated | An operative wound in which the respiratory, alimentary, genital, or urinary tracts are entered under controlled conditions and without unusual contamination.  Specifically, operations involving the biliary tract, appendix, vagina, and oropharynx are included in this category, provided no evidence of infection or major break in technique is encountered. |
| Class III/ Contaminated | Open, fresh, accidental wounds.  In addition, operations with major breaks in sterile technique (e.g., open cardiac massage) or gross spillage from the gastrointestinal tract, and incisions in which acute, non-purulent inflammation is encountered are included in this category. |
| Class IV/ Dirty-Infected | Old traumatic wounds with retained devitalized tissue and those that involve existing clinical infection or perforated viscera.  This definition suggests that the organisms causing postoperative infection were present in the operative field before the operation |

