## Description of study evaluations/measurements/assessments

## Primary Endpoint

The rate of surgical site infection till 30 days after surgery (90 days if implant) using CDC definition of SSI in pre-intervention versus post-intervention phase for clean, clean-contaminated and contaminated surgeries (Annexure-II, III).

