## Statistical analysis plan

The data collected in the antimicrobial audit form will be analysed after entry into the excel form. The antimicrobial consumption analysis will be done using Microsoft excel. The descriptive data analysis will be done using Statistical package for the social sciences (SPSS) Version 23. The rate of surgical site infection till 30 days after surgery (90 days if implant) will be expressed as events per person-time, separately for clean, clean-contaminated, contaminated surgeries. All secondary endpoints will be expressed as mean, standard deviation (if the variable is quantitative) or as frequency, percentage (if the variable is categorical). The rates of primary outcome and secondary outcomes measured at the study centres in post-intervention will be compared with the pre-intervention/baseline data to assess the impact of the intervention. Chi-square test, independent sample t test or Mann-Whitney U test will be used for the statistical comparisons.

Plots and pivot tables will be generated using statistical software or excel as appropriate. The analysis will be conducted separately for clean, clean-contaminated and for contaminated surgeries. A sub-group analysis will also be conducted as per the level of fidelity.

Kaplan Meier curves will be plotted to demonstrate the incidence rates of surgical site infections. The difference in the rate of surgical site infections between the nature of surgeries (clean, clean-contaminated, contaminated surgeries), or any other exposure categories will be statistically tested using the log-rank test. A Cox proportional hazard model will be constructed to identify the predictors of surgical site infections.

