## Sample Size and Power

The three strata based on the type of the surgery (clean, clean-contaminated and contaminated) will be separately powered, based on different baseline SSI rates extracted from Indian study showing prevalence of SSIs in general surgery patients.^7,8^ The sample sizes were based on 90% power, a 5% two-sided significance level and 15% loss to follow up or death before reaching the primary endpoint at 30-days. For the clean surgeries, anticipating the baseline average SSI rate of 8%, a 3% absolute reduction in SSI to 5% will be taken as clinically significant and would require 3260 patients in total (1630 patients in pre-intervention and intervention each). For the clean-contaminated surgeries, anticipating the baseline average SSI rate of 12%, a 4% absolute reduction in SSI to 8% will be taken as clinically significant (i.e relative risk of 0.67) and would require 2700 patients in total (1350 in pre-intervention and intervention each). For the contaminated surgeries, anticipating higher baseline SSI rate of 30%, a 10% absolute reduction in SSI to 20% will be taken as clinically significant and would require 900 patients in total (450 in pre-intervention and intervention each).

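### The primary SSI comparison is made only within final wound class, which is partly settled during surgery, and no planned pre/post comparison would correct for a change in how operations are classed

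*Protocol*

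**What the plan says.** Protocol section 3.7 defines the primary endpoint as the SSI rate "in pre-intervention versus post-intervention phase for clean, clean-contaminated and contaminated surgeries". Section 3.9 states: "The analysis will be conducted separately for clean, clean-contaminated and for contaminated surgeries". Section 3.11 powers each class on its own, with 1630, 1350 and 450 patients per phase for clean, clean-contaminated and contaminated surgery.

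Appendix IV defines the classes. Biliary, appendiceal, vaginal and oropharyngeal operations are Class II only if there is no infection and no major break in technique. Class III includes "operations with major breaks in sterile technique (e.g., open cardiac massage) or gross spillage from the gastrointestinal tract". It also includes fresh accidental wounds and incisions showing acute non-purulent inflammation.

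Under section 4.1 the infection control nurse and research fellow record the class on the data form in both phases. The section does not say when in the operation the class is assigned or by what procedure. Section 3.2 gives blinding as not applicable.

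The intervention is still to be co-developed (section 3.1.2). The template in Appendix I, Table-2 includes an item that ends with "aseptic precautions including hand hygiene" and another on limiting door opening. Both are typed optional.

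**The concern.** A stratum boundary that can move between phases weakens a before/after comparison made only inside the strata. Take two similar biliary operations, one in each phase. If one is classed contaminated because of a major break and the other clean-contaminated, they enter different comparisons. This could happen because a break was avoided, or because the same events were recorded differently.

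Each stratum's difference would then combine the effect on infection with a change in who is in the stratum. The result could look like a benefit or a harm, or could hide a benefit.

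Section 3.9 contains nothing that would separate the two. Its log-rank test compares wound classes or other exposure categories, and its Cox model looks for predictors of SSI. Neither names phase as the comparison. A model of phase adjusted for final class would still condition on the same variable.

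**Working it through.** **Inputs from section 3.11.** "The sample sizes were based on 90% power, a 5% two-sided significance level and 15% loss to follow up or death". Planned SSI rates are 8% to 5% (clean), 12% to 8% (clean-contaminated) and 30% to 20% (contaminated), with 1630, 1350 and 450 patients per phase.

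**The plan's own figures.** The pooled-variance two-proportion formula gives 1418, 1181 and 392 evaluable patients per phase. Multiplied by 1.15 these become 1631, 1359 and 451, against the stated 1630, 1350 and 450. The sizes reproduce and can serve as the base.

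**Assumed inputs (not in the documents).** A fraction *f* of operations that baseline practice would class as II is classed as III in the post phase. These cases have SSI risk *r*. No patient's true risk changes.

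**Stratum rates after recoding.**
- Class II: (0.12 × 1350 − r·f·1350) / (1350 × (1 − f))
- Class III: (0.30 × 450 + r·f·1350) / (450 + f·1350)

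For f = 10% and r = 20%, 135 cases with 27 infections move:
- Class II: (162 − 27)/1215 = 11.1%
- Class III: (135 + 27)/585 = 27.7%

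The apparent falls are 0.89 and 2.31 points, which is 22% and 23% of the planned 4- and 10-point effects.

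**Rejection probability.** With 85% evaluable, d the pre/post difference, se0 the pooled and se1 the unpooled standard error, it is Φ((d − 1.96·se0)/se1) + Φ((−d − 1.96·se0)/se1).
- Class II (1147.5 vs 1032.75 patients): d = 0.00889, se0 = 0.01372, se1 = 0.01370, giving 9.9%.
- Class III (382.5 vs 497.25 patients): d = 0.02308, se0 = 0.03076, se1 = 0.03085, giving 11.7%.

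| Recoded share of Class II | Risk in recoded cases | Class II rate | Rejection | Class III rate | Rejection |
|---|---|---|---|---|---|
| 1% | 20% | 11.9% | 5.0% | 29.7% | 5.1% |
| 3% | 20% | 11.8% | 5.4% | 29.2% | 5.8% |
| 5% | 20% | 11.6% | 6.1% | 28.7% | 7.0% |
| 10% | 20% | 11.1% | 9.9% | 27.7% | 11.7% |
| 10% | 15% | 11.7% | 5.6% | 26.5% | 20.6% |
| 10% | 25% | 10.6% | 18.5% | 28.8% | 6.6% |

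For 1–3% recoded and a risk of 15–25%, every value lies between 5% and 7%.

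**Opposite direction.** Suppose 10% of Class III (45 cases) is classed as II in the post phase, again with no true effect.
- At 15% risk: Class III is (135 − 6.75)/405 = 31.7% and Class II is (162 + 6.75)/1395 = 12.1%.
- At 40% risk: Class III is (135 − 18)/405 = 28.9% and Class II is (162 + 18)/1395 = 12.9%.

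Class III can therefore move either way, while Class II rises whenever the moved cases carry more than its 12% baseline risk. If 5% of Class III moves, the shifts stay below one point.

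**All classes together.** At the planned baseline mix the rate is (130.4 + 162 + 135)/3430 = 427.4/3430 = 12.5%. Relabelling among Classes I to III leaves it unchanged.

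**The case against.** Several stronger readings are tempting, and the documents do not support them.

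- **A reader might infer that the intervention targets the breaks that define Class III.** Table-2 is a template. Its asepsis wording closes an optional skin-preparation item, and no component addresses major breaks or gastrointestinal spillage. Most items, such as prophylaxis timing, hair removal, glucose and temperature, cannot change wound class. The package may affect class, but no more than that can be said.
- **A reader might infer that training will lead staff to record more breaks.** No section describes training in recognising breaks or coding class, and section 3.1.4 collects the same parameters in both phases. What stands is that recording is unblinded and the assignment procedure is not fixed. Section 3.1.3 also allows an infection control nurse to be the champion of the intervention at a site.
- **A reader might infer that patients change stratum.** The phases enrol different patients. At most, similar operations are classed differently.
- **A reader might take the 10–12% rejection figures as expected.** They require 135 extra cases in a Class III of 450, a 30% expansion, which would show in the stratum counts if enrolment is not capped by class. Fresh accidental wounds and acute inflammation also lead to Class III and owe nothing to technique.
- **A reader might conclude that expected class should replace final class in the primary analysis.** Breaks and spillage cannot be foreseen, so an expected Class III would be smaller. If 30% of it (an assumed share) arose from such events, 450 would become about 315 per phase. With 85% evaluable, power for 30% versus 20% would fall from about 89% to 76%.

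Supporting analyses can be left to a statistical analysis plan. The expected class cannot: it has to be collected from the first baseline patient, because it cannot be reliably reconstructed later.

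**Conclusion.** The point holds as a gap in protection. It does not show that the results will be biased. The primary comparison exists only within a class that is partly decided during surgery and recorded without blinding, and no stated pre/post analysis is immune to a change in classing. The direction of any distortion is unknown, and its size depends on shares and risks that the documents do not give. Under the assumptions above it is small at 1–3% recoding of Class II and material near 10%. The remedy is cheap enough to be worth adopting despite that uncertainty.

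**What to change.** Keep final CDC class as the primary stratifier, and make three additions:

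1. From the start of baseline, add one field to the case record form: the wound class expected for the planned procedure, recorded at the pre-operative screening that section 4.4 already provides for.
2. In section 3.9, add one all-class pre/post SSI comparison stratified by expected class, as a prespecified supporting analysis.
3. Tabulate expected against final class by phase.

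The cost is one field and one extra analysis. Expected class will be less certain in emergency cases. The all-class comparison is protected from relabelling only if enrolment within a phase is not stopped by quotas on final class, so the protocol should state how enrolment in each phase ends. It does not cover movement into or out of the dirty class, which is excluded from the study.
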